### Potential Limitations and Solutions

The results from Aims 1 and 2 will be used to refine the intervention for Aim 3. For example, if we find that the PCP prefers to communicate with the school nurses via secure email instead of by phone, we will adjust the procedures. If the school nurses have issues accessing the data, I can offer additional training. As self-reports of adherence may be inflated, we will compare medication counts with information entered into the app by the parent or caregiver. Finally, even though AMD-Sp is easy to use and will require approximately five minutes of the parent’s or caregiver’s time to log symptoms and medication adherence information, if the parent or caregiver is having difficulty using the technology, my bilingual research assistant will provide additional support. I will be tracking app usage for the first week of each new enrollee to discuss concerns and strategies. We are aware of the possibility that these participants may have some unknown difficulties. If this preliminary step reveals this to be an issue, we can consider simple modifications to the study plan, such as the use of a short messaging service (ie, text messaging, which is associated with improved chronic disease management) in lieu of the app.

### Aim 3: Investigate the Feasibility of the Patient-Centered Asthma Intervention

#### Overview

With the results from Aim 2, I will refine the collaborative intervention and produce the protocol to be utilized in Aim 3. Using a waiting-list RCT, I will then evaluate the feasibility and acceptability of the intervention, including dosing, fidelity, recruitment, and retention [29], and investigate the effects of the intervention on school days missed and medication adherence.

#### Participant Recruitment

Participant recruitment will occur on a rolling basis and will follow the same procedure as noted in Aim 2, except that 20 Latino families will be recruited, following the same inclusion and exclusion criteria, for this arm of the study. Participant responsibilities will also remain as noted in Aim 2, unless there is a need to modify them based on the qualitative results from Aim 2. As the families are enrolled in the study, they will be randomly assigned to either the intervention group or the waiting-list control group. After the initial 10 intervention group participants complete the 6-month data collection period, the 10 waiting-list control group participants will then proceed with the 6-month intervention. In addition to [name], there are additional pediatricians and nurse practitioners at the primary care clinic site, as well as other pediatric providers in the area served by the LCSD. An invitation to participate will be extended to them as well. Participant training will follow the procedures outlined previously. At the completion of the study, parents and guardians will receive US $100 cash per family.

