#### Intervention

The refined protocol developed at the end of Aim 2 will be used to direct the intervention stage of Aim 3; it is anticipated that the steps will be similar. Participants will be followed for 6 months.

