#### Data Collection

Anticipated quantitative data that will result from Aim 3 include the information entered into the app by the parent or caregiver, which are then encrypted and transmitted to the school nurse. These data will include selected NIH and Agency for Healthcare Research and Quality standardized asthma outcomes [30], including the primary outcome measures of medication adherence information (ie, asthma medication ratio [31], which is predictive of childhood asthma ED visits and hospitalizations) and school days missed. This school district requires HIPAA waivers to allow communication between school nurses and local health care providers and will be able to provide information on recorded school absences once informed consent forms are obtained. Secondary outcome measures include frequency of rescue inhaler use, as well as asthma exacerbations, outpatient clinic visits, and ED visits (see Table 2). Lung capacity will be obtained using spirometry pre- and postintervention [32] to obtain relevant lung function variables, such as FEV1 (forced expiratory volume in 1 second) and FEV1/FVC (forced vital capacity). Measures from the control group will include medication counts, number of asthma exacerbations, ED and outpatient clinic visits, and spirometry measures on enrollment, during the intervention phase, and again at the end of the intervention.

**Table 2 table2:** Outcome measures and their details.

Outcome variable	Description	Source of data	Type of measure
Medication adherence—asthma medication ratio (primary outcome)	Medication administration data uploaded to the app	Parents	Continuous
Medication adherence—asthma medication ratio (primary outcome)	Medication counts performed monthly by the principal investigator	Principal investigator	Continuous
School days missed	School absences secondary to asthma symptoms	Nurses	Continuous
Asthma exacerbations	Number of asthma exacerbations uploaded to the app	Parents	Continuous
Frequency of rescue inhaler use	Albuterol usage for wheezing episodes	Parents	Continuous
Emergency department visits	Number and dates of emergency department visits uploaded to the app	Parents	Categorical
Outpatient clinic visits	Number and dates of outpatient clinic visits uploaded to the app	Parents	Continuous

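### The waiting-list comparison has no fixed control window: rolling randomisation with a group-level crossover gives controls unequal waits, and event outcomes carry no period or denominator

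*Protocol article*

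**What the plan says.** Under Aim 3, Participant Recruitment, the protocol article sets three rules.

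- Entry is staggered: "Participant recruitment will occur on a rolling basis".
- Allocation happens at entry: "As the families are enrolled in the study, they will be randomly assigned to either the intervention group or the waiting-list control group".
- Crossover depends on the intervention group as a whole: "After the initial 10 intervention group participants complete the 6-month data collection period, the 10 waiting-list control group participants will then proceed" with their own 6 months of intervention.

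Under Aim 3, Intervention, it says "Participants will be followed for 6 months". It does not say whether this covers the waiting period, the intervention period or both.

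Under Aim 3, Data Collection, the list for controls opens "Measures from the control group will include medication counts, number of asthma exacerbations, ED and outpatient clinic visits" and ends with "spirometry measures on enrollment, during the intervention phase, and again at the end of the intervention". The same section names school days missed as a primary outcome measure, alongside the asthma medication ratio.

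Table 2 describes exacerbations as "Number of asthma exacerbations uploaded to the app" and clinic visits as "Number and dates of outpatient clinic visits uploaded to the app", and types both as Continuous. Emergency department visits have the same kind of description (a number with dates) but are typed Categorical. School days missed are typed Continuous. No event outcome has a stated period or denominator.

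**The concern.** The clock that starts a control's observation belongs to the individual family; the clock that ends it belongs to the other arm. An early control waits until the tenth intervention family has finished. A control who enrols after the last intervention family becomes due to cross over before completing 6 months.

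The timing of control assessments does not repair this. If the intervention phase means that of the intervention group, the last control assessment falls at a different elapsed time for each child. If it means the control's own later intervention, no assessment at the end of the wait is stated. Neither reading gives a control measurement 6 months after that child's randomisation.

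This matters most for outcomes that grow with observation time: school days missed, exacerbations, rescue use and visits. The Power Analysis section says the study's goal is effect size estimates for future work, so a difference created by unequal exposure could carry into the design of the next trial.

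**Working it through.** **1. The plan's own power figure.** Inputs: 10 per group (Power Analysis), one-sided 0.05 (Statistical Analysis). For a two-sample t test with 18 degrees of freedom, the critical value is 1.734 and the noncentrality is d × √(10/2).
- d = 0.80: noncentrality 1.789, power 0.530 (stated .53).
- d = 1.16: noncentrality 2.594, power 0.802 (.80 is implied).

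The stated figures reproduce. They concern the asthma medication ratio, and this point does not change them.

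**2. How long controls wait.** Control wait = (enrolment time of the last intervention family + 6) − own enrolment time. The recruitment length R is not given, so it is an assumption here. With enrolment uniform over R months and 10:10 random allocation, the last of 10 intervention families enrols on average at (10/11)R and a control at R/2. So

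mean wait = 6 + R(10/11 − 1/2) = 6 + 0.409R.

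The earliest of 10 controls enrols on average at R/11, so the longest wait averages 6 + (9/11)R.

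| Assumed R (months) | Mean wait | Ratio to 6 months | Mean longest wait |
|---|---|---|---|
| 3 | 7.2 | 1.20 | 8.5 |
| 6 | 8.5 | 1.41 | 10.9 |
| 12 | 10.9 | 1.82 | 15.8 |

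Evenly spaced enrolment gives slightly longer mean waits: 7.4, 8.7 and 11.4 months.

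**3. Who waits less than 6 months.** A control does so when it enrols after all 10 intervention families. Among those 11 families each is equally likely to be last, so the probability is 1/11 = 9.1%. At least one such control exists whenever the last of the 20 families is a control, which has probability 1/2. Neither result depends on R, provided enrolment is staggered.

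**4. What follows if the whole wait is counted.** This is an illustration by simulation with no true effect. Assumptions: evenly spaced enrolment; a mean of 2 or 4 events per 6 months; Poisson counts, or gamma-Poisson counts with shape 1.5; one-sided 0.05 t test on totals. The article names no test for these outcomes.

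| Assumed R (months) | False-positive rate, whole wait counted |
|---|---|
| 3 | 0.10 to 0.23 |
| 6 | 0.17 to 0.49 |
| 12 | 0.33 to 0.84 |

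With the first 6 months from enrolment used in both arms, the rate is 0.045 to 0.054 throughout.

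**5. School calendar.** Assume 180 school days spread evenly over weekdays from 17 August to 4 June. A 6-month window then holds between 68 and 111 school days, depending on its starting month. A raw count of absences therefore has a different opportunity from child to child, even with equal windows.

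**The case against.** A reader might infer that control follow-up exceeds 6 months and that the count outcomes are therefore biased in favour of the intervention. The article does not support that as a statement of fact.

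- Waiting time is not analysed follow-up. Nothing says that control events are totalled over the whole wait. The 6-month follow-up statement can be read as a 6-month window in both arms, and step 4 shows no inflation on that reading.
- The wait is not above 6 months for every control; about 9% fall short.
- The direction is not certain. Most event outcomes are uploaded to the app by parents, and the article does not say whether waiting families have the app. Under-recording in controls would work against the intervention, and extra waiting time in summer adds no absences.
- The calendar is not a source of bias in the first 6 months. Allocation is concurrent, so both arms cover similar calendar time in expectation. What remains is noise, plus any extra waiting time.
- The main analysis compares average adherence, and the asthma medication ratio does not accumulate with time.
- A Continuous label does not itself show that totals over unequal periods are compared, and the choice of count model can be left to an analysis plan.

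All of this stands, and it makes the bias conditional. It does not remove the underlying problem: the stated rules themselves produce unequal control periods, no stated control assessment at a matched time, and no common exposure for an outcome named as primary. Reading the follow-up statement as a 6-month window also fails for controls who become due to cross over before 6 months.

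**Conclusion.** The point holds as a design inconsistency. Rolling randomisation, a group-level crossover trigger and control assessments tied to the intervention phase do not fit together with a single 6-month follow-up. Under staggered enrolment the mean control wait is above 6 months (6 + 0.409R if enrolment is uniform), and 1 control in 11 is expected to wait less.

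Bias in school days missed and the other event outcomes is possible, usually in favour of the intervention, but only if the whole wait is counted. The article neither says so nor rules it out. The main asthma medication ratio comparison is largely unaffected.

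The wait lengths rest on the assumed recruitment period. The false-positive rates rest also on assumed event rates, dispersion and test, so they show what could happen and do not predict this trial's error rate. The separate labelling fault needs no assumption: two outcomes described in the same way, as numbers with dates of visits, are given different measurement types.

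**What to change.** - Reconcile Participant Recruitment, Intervention and Data Collection, so that the between-group comparison uses the first 6 months after each family's own randomisation date in both arms. Place the end-of-period control assessment, including spirometry, at that point.
- Reconcile the crossover timing with this window, so that the window is complete for every control. Otherwise, cut the control's data at crossover and carry the shorter exposure as an offset.
- Type all event outcomes, including emergency department visits, as counts. Compare them as rates per time observed, and absences per school day in session.

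**Cost.** Mostly wording. Medication counts are already monthly, and emergency department and clinic visits already carry dates, so these can be cut to the window. Control spirometry must be re-timed, which may add a visit for some controls, and the rate analysis is slightly more work. The change should be made before enrolment starts, because a spirometry measurement not taken at 6 months cannot be recovered later.

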#### Intervention

The refined protocol developed at the end of Aim 2 will be used to direct the intervention stage of Aim 3; it is anticipated that the steps will be similar. Participants will be followed for 6 months.

#### Data Collection

Anticipated quantitative data that will result from Aim 3 include the information entered into the app by the parent or caregiver, which are then encrypted and transmitted to the school nurse. These data will include selected NIH and Agency for Healthcare Research and Quality standardized asthma outcomes [30], including the primary outcome measures of medication adherence information (ie, asthma medication ratio [31], which is predictive of childhood asthma ED visits and hospitalizations) and school days missed. This school district requires HIPAA waivers to allow communication between school nurses and local health care providers and will be able to provide information on recorded school absences once informed consent forms are obtained. Secondary outcome measures include frequency of rescue inhaler use, as well as asthma exacerbations, outpatient clinic visits, and ED visits (see Table 2). Lung capacity will be obtained using spirometry pre- and postintervention [32] to obtain relevant lung function variables, such as FEV1 (forced expiratory volume in 1 second) and FEV1/FVC (forced vital capacity). Measures from the control group will include medication counts, number of asthma exacerbations, ED and outpatient clinic visits, and spirometry measures on enrollment, during the intervention phase, and again at the end of the intervention.

**Table 2 table2:** Outcome measures and their details.

Outcome variable	Description	Source of data	Type of measure
Medication adherence—asthma medication ratio (primary outcome)	Medication administration data uploaded to the app	Parents	Continuous
Medication adherence—asthma medication ratio (primary outcome)	Medication counts performed monthly by the principal investigator	Principal investigator	Continuous
School days missed	School absences secondary to asthma symptoms	Nurses	Continuous
Asthma exacerbations	Number of asthma exacerbations uploaded to the app	Parents	Continuous
Frequency of rescue inhaler use	Albuterol usage for wheezing episodes	Parents	Continuous
Emergency department visits	Number and dates of emergency department visits uploaded to the app	Parents	Categorical
Outpatient clinic visits	Number and dates of outpatient clinic visits uploaded to the app	Parents	Continuous

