#### Training

##### Primary Care Provider and School Nurses

I will conduct one-on-one sessions with the PCP and school nurses to explain how the patient enters information (ie, medication administration and symptoms) into the app. For the school nurses, I will demonstrate how to access the digitally encrypted information using their site-based computers, which are available at all LCSD schools, as well as provide a short manual of instructions that will include screenshots and frequently asked questions.

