##### Quantitative Data Collection

We will perform medication counts monthly; asthma medications that do not have counters or individual vials, such as some metered-dose inhalers, will be fitted with a PuffMinder, a digital inhaler dose counter. These results will be compared to the self-report medication adherence information entered into the app by the parent or caregiver.

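### The principal investigator, who very probably knows each family's arm, makes the medication counts meant to check self-reported adherence, so that check is open to detection bias

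*Protocol article*

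**What the plan says.** In the protocol article, Table 2 (Aim 3, Data Collection) has two rows labelled "Medication adherence—asthma medication ratio (primary outcome"). One takes its data from what parents enter in the app. The other is described as "Medication counts performed monthly by the principal investigator", and its source column also names the principal investigator. School days missed is named as a primary measure in the text above the table and comes from the nurses.

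For the waiting-list group, the same section states: "Measures from the control group will include medication counts, number of asthma exacerbations, ED and outpatient clinic visits, and spirometry measures". App adherence entries are not in that list.

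The reason for counting is given under Potential Limitations and Solutions: "As self-reports of adherence may be inflated, we will compare medication counts with information entered into the app by the parent or caregiver".

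The principal investigator's other roles are also stated:
- On the design of the intervention (Aim 3, Overview): "I will refine the collaborative intervention and produce the protocol to be utilized in Aim 3".
- On training (Aim 2, Training): "I will conduct one-on-one sessions with the PCP and school nurses". Aim 3, Participant Recruitment, carries the training procedures forward.
- Under Potential Limitations and Solutions, the principal investigator follows each new enrollee's app use in the first week.
- Under Data Security, parents send their app data to the school nurse and the principal investigator.

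On equipment, the Aim 2 section Quantitative Data Collection says that medications with neither a counter nor individual vials "will be fitted with a PuffMinder, a digital inhaler dose counter".

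**The concern.** A count that checks self-report should not depend on someone with a stake in the result who knows which arm is being counted. Here the developer of the intervention is the named assessor of the count-based version of a primary outcome.

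The exposure is greater because, as written, the counts are the only adherence measure listed for both arms. The main Aim 3 analysis compares average adherence between the groups, so it rests largely on these readings. Any difference in how the two arms are counted enters that comparison in full. With 10 families per arm it could be neither detected nor averaged out.

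Two things are at stake: the chance of a false-positive result, and the effect size estimate that the Power Analysis section names as the study's goal.

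**Working it through.** **1. Who counts, and what that person knows.** Table 2 names the principal investigator. Data Security makes that person a recipient of the app data. Participant Recruitment (Aim 3) has waiting-list families start the intervention only after the first group has finished its 6 months. A family sending app data in the first period is therefore recognisably in the intervention arm. Knowledge of allocation is an inference from these passages, but a firm one.

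**2. Reproduce the plan's own figures, to fix the test.** Inputs are 10 per group (Power Analysis) and a one-sided .05 level (Statistical Analysis). For a two-sample t test, which a regression on group alone reproduces, the degrees of freedom are 10 + 10 − 2 = 18 and the critical value is 1.734. The noncentrality is d × √(10/2) = 2.236 d.

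| d | noncentrality | power | stated |
|---|---|---|---|
| 0.80 | 1.789 | .530 | .53 |
| 1.16 | 2.594 | .802 | no power given in that clause; .80 in the sentence before |

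Both figures reproduce with the one-sided t test. The two-sided test gives .395 and .689, so the plan's figures are one-sided.

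**3. Same test, no true effect, differential counting shift b in SD units.** The rejection rate is P(T > 1.734), where T is noncentral t with 18 df and noncentrality 2.236 b.

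| b (SD) | noncentrality | false-positive rate |
|---|---|---|
| 0 | 0 | .050 |
| 0.05 | 0.112 | .062 |
| 0.1 | 0.224 | .076 |
| 0.2 | 0.447 | .112 |
| 0.4 | 0.894 | .217 |

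**4. On the scale of the ratio.** The documents give no SD, so 0.25 is assumed, with a range of 0.20 to 0.30.
- A shift of 0.05 is 0.05/0.25 = 0.2 SD, giving .11. Over the SD range it is 0.17 to 0.25 SD, giving about .10 to .13.
- A shift of 0.10 is 0.10/0.25 = 0.4 SD, giving .22. Over the SD range it is 0.33 to 0.50 SD, giving about .18 to .28.

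**5. Effect on the estimate.** The expected observed effect is the true effect plus b. A shift of 0.2 SD is 0.2/0.80, a quarter of the effect that the plan calls large.

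The shifts are chosen for illustration. Nothing in the documents says how large a counting difference would be, or that there is one.

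**The case against.** The strongest reply is that these counts are mostly readings of a number or a tally of vials. The PuffMinder text stands under Aim 2, but Aim 3 expects similar steps. Reading a display leaves little room for judgment. This stands: it limits the likely size of any bias, and it makes documentation cheap. It does not cover which devices are presented and listed, or how refills are assigned to a period. The article does not describe these steps, so their weight is also unknown.

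Several stronger readings are tempting, and the documents do not support them:
- That the article declares the principal investigator unblinded. It does not mention blinding, and the full protocol may address it. The finding is the stated choice of counter, not that silence.
- That the principal investigator alone counts. Table 2 points to one person, but the Aim 2 text uses the plural.
- That the principal investigator trains the families being counted. A bilingual research assistant does that; the principal investigator trains the provider and nurses.
- That every primary outcome is affected. App entries are a second source for the ratio, and school days missed comes from the nurses.
- That the counts are biased, or that the error rate is .11 or .22. These figures follow only from assumed shifts.

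It is also fair that the list of control-group measures may not be exhaustive, and that this is an admittedly underpowered feasibility study with no confirmatory claim. But its goal is an effect size estimate, which is what a shift would distort.

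**Conclusion.** The point holds in a limited form. The plan assigns its check on inflated self-report to the person who refines the intervention and almost certainly knows allocation. That check is therefore open to detection bias. Bias is not shown and may be small.

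Assumed differential shifts of 0.1, 0.2 and 0.4 SD would raise the one-sided .05 error rate to about .08, .11 and .22 and would add the same amount to the estimated effect. The rates in SD units rest on normal data, equal variances and 10 per arm. Their translation to units of the ratio rests on an assumed SD. No sample size or power figure in the plan changes.

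Priority is low to moderate. The case for acting is that the remedy is cheap and that readings not documented at the visit cannot be recovered later.

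**What to change.** In Aim 3, Data Collection, and in Table 2, state the following:
1. At each monthly count, in both arms, all controller and rescue devices are listed on a fixed form. Each counter, PuffMinder display or set of vials is photographed with a date and filed by study ID only.
2. The rules for refills and missing devices are set before data collection starts.
3. A current team member without the arm code derives the ratio from the coded readings before the arm code is merged. The article names no analyst, so the team has to say who this is.
4. The principal investigator's tally is used for reconciliation only.

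The cost is wording, a few minutes per visit and image storage. The counts are already planned monthly, so no visit is added. The limit is that photographs do not capture devices that are never produced. The form and the pre-set rules narrow the discretion over what is listed but do not remove it.

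### School days missed, named as a primary outcome in the text, rests in Table 2 on asthma attribution reported by nurses who take part in the intervention, and it is not among the listed control-group measures

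*Protocol article*

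**What the plan says.** The article makes the effect on school days missed a target of Aim 3 in the abstract, the Study Overview and the Aim 3 Overview. The Data Collection section places it among the primary outcome measures, where the list ends with "hospitalizations) and school days missed".

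Table 2, in the same section, differs in two ways. The primary-outcome label stands only on the two asthma medication ratio rows. School days missed is defined by cause, as "School absences secondary to asthma symptoms", with nurses as the data source. No rule is given for deciding that an absence was due to asthma.

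The text also mentions a second source: the school district "will be able to provide information on recorded school absences once informed consent forms are obtained". That sentence is not limited to one arm and does not mention reasons for absence. Table 2 does not use this source.

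For controls, the article states: "Measures from the control group will include medication counts, number of asthma exacerbations, ED and outpatient clinic visits, and spirometry measures on enrollment", with further measurement during and at the end of the intervention phase. School absence is not in the list.

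On the nurses' role, the Aim 3 data are described as "information entered into the app by the parent or caregiver, which are then encrypted and transmitted to the school nurse". The Aim 2 training section says "For the school nurses, I will demonstrate how to access the digitally encrypted information using their site-based computers", and the Aim 3 recruitment section carries this over: "Participant training will follow the procedures outlined previously". Controls start the intervention only after the first 10 intervention participants have completed 6 months.

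**The concern.** A cause-specific absence count needs someone to decide, or to pass on, why the child was away. The named source is a nurse who is part of the intervention. For a child using the app, the nurse has symptom and medication entries in English. For a waiting-list child whose caregiver prefers Spanish, the nurse may have much less to go on. If so, the share of true asthma absences that are counted as such depends on arm, and the between-group comparison mixes the effect of the intervention with a difference in ascertainment.

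The control list raises a separate problem. If controls truly have no absence data, the between-group effect cannot be estimated at all. These two defects cannot both apply in full, because ascertainment can differ by arm only if control data exist. The article leaves open which one applies.

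The Power Analysis section says that the goal is effect size estimates for future work. A ratio distorted by ascertainment would pass straight into the next trial's design, and a larger sample there would not correct it.

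**Working it through.** **The plan's own figures.** The only power figures concern the asthma medication ratio. A two-sample t-test with 10 per group and one-sided alpha 0.05 gives power 0.530 at an effect size of 0.80 (stated: .53) and 0.802 at 1.16. Both are consistent with the article. Neither bears on school days missed, for which no figure is given.

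**The statements side by side.**

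| Item | Data Collection text | Table 2 |
|---|---|---|
| Status | Primary outcome measure | No primary label |
| Definition | School days missed; recorded absences obtainable | Absence due to asthma |
| Source | School district | Nurses |
| Control group | Not in the list of control measures | Not stated by arm |

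**Effect of unequal attribution.** Let R be the true ratio of asthma absences (intervention to control), and let s_I and s_C be the proportions of true asthma absences counted as such in each arm. Ignoring false attribution, the observed ratio is R × s_I / s_C. The documents give none of these inputs, so all values below are assumptions.

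| R | s_I | s_C | Observed ratio |
|---|---|---|---|
| 1.00 | 0.90 | 0.60 | 1.50 |
| 1.00 | 0.60 | 0.90 | 0.67 |
| 0.70 | 0.80 | 0.60 | 0.70 × 0.80/0.60 = 0.93 |
| 0.70 | 0.90 | 0.60 | 0.70 × 0.90/0.60 = 1.05 |
| 0.70 | 0.60 | 0.90 | 0.70 × 0.60/0.90 = 0.47 |

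**Effect on the test.** A simulation assumed no true effect, 10 children per arm, gamma-mixed Poisson counts (shape 2) with a mean of 2, 4 or 6 asthma absences in 6 months, and a one-sided t-test for benefit at 0.05, with 20,000 trials per scenario.

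| s_I / s_C | Mean 2 | Mean 4 | Mean 6 |
|---|---|---|---|
| 0.70 / 0.70 | 4.9% | 5.1% | 5.0% |
| 0.90 / 0.60 | 0.8% | 0.5% | 0.5% |
| 0.60 / 0.90 | 18.7% | 23.0% | 25.2% |

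Entries are the percentage of trials that declare a benefit. Equal attribution keeps the nominal 5%. Unequal attribution moves the rate far below or far above it, depending on which arm is better ascertained.

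**Cost of the arm-neutral measure.** Let p be asthma's share of all absences in controls, with other absences unaffected by the intervention. The all-cause ratio is then 1 − p × (1 − R). With R = 0.70:

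- p = 0.10: 1 − 0.10 × 0.30 = 0.97
- p = 0.25: 1 − 0.25 × 0.30 = 0.925, about 0.93
- p = 0.50: 1 − 0.50 × 0.30 = 0.85

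The share p is also an assumption.

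**The case against.** A reader might infer that this outcome is shown to be biased and that the bias hides a real benefit. The documents do not support that, for three reasons.

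- Table 2 names nurses only as the data source. It does not say that they judge the cause; a nurse could pass on a reason given by the parent.
- No sentence says that nurses see app data for intervention children only. That is inferred from the waiting-list design. The control list contains exacerbations and emergency and clinic visits, which Table 2 draws from app entries by parents, so how control data reach the study is itself unclear.
- Better recognition of asthma absences in the intervention arm is plausible, because the app is meant to ease communication between nurse and family. It is not established, and the reverse pattern would produce a false benefit.

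A reader might also infer that controls will have no absence data. The wording of the control list need not be exhaustive, the article is condensed, Aim 3 states the comparison, and the district sentence covers both arms. Collection in controls is probably intended.

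Finally, this is a feasibility study of 20 families. The main analysis and the power statement concern adherence, and switching to all-cause absence would exchange a bias risk for dilution.

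These arguments limit the claim to a risk and make the choice of measure a trade-off. They do not reconcile the text with Table 2, and they supply neither an attribution rule nor a control-group entry. These are not details left to another document: the article itself fixes the definition, the source and the control measures, and they do not fit together.

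**Conclusion.** The point holds as a risk of differential ascertainment, together with an internal inconsistency. Certain from the text are the conflict over primary status, the cause-specific definition with nurses as source, the nurses' part in the intervention, and the absence of the outcome from the control list. Inferred is that nurses have app data mainly for intervention children during the comparison period.

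The direction and size of any bias cannot be fixed from the documents. Under the assumed attribution rates of 60% and 90%, the apparent ratio with no true effect lies between 0.67 and 1.5, and the chance of declaring a benefit runs from under 1% to about 25% instead of 5%. Taken literally, the control list would make the between-group effect inestimable; that is a separate defect from bias and probably an omission in the listing.

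**What to change.** 1. Add school absences to the control-group measures.
2. Obtain district-recorded absences for both arms over the same 6 months after randomisation, closing before a control child starts the intervention. Express them per school day in session, because rolling recruitment gives children different numbers of school days in the window. This is the arm-neutral measure.
3. Report asthma-attributed absence beside it, with one written attribution rule and the same information source in both arms, applied without knowledge of arm where possible. App entries available for one arm only should not feed the attribution.
4. Make the text and Table 2 agree on whether school days missed is a primary outcome, and on its definition and source.

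The cost is mainly wording, plus consent forms in both arms that cover attendance records, since the district supplies them only after consent. The sample size and the stated power figures do not change. The real downside is dilution: all-cause absence can shrink a true asthma ratio of 0.70 to between 0.85 and 0.97 under the assumed shares, which is hard to see with 10 per arm. For that reason both measures should be reported, and all-cause absence should not simply replace the asthma-specific one.
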